##### Generalizability

To assess generalizability, socio-demographics (e.g. age, educational level and household status) and medical information (e.g. diagnosis, tumour type, disease stage, type of treatment and comorbidity) of the UMBRELLA Fit study population will be compared to characteristics of more than 3163 patients with breast cancer participating in exercise trials, available from the POLARIS database with individual patient data from 34 international exercise-oncology trials [10]. Socio-demographical information on the UMBRELLA Fit study population is registered in, and obtained from the UMBRELLA cohort. Medical information is obtained from the Netherlands Cancer Registry (NCR), which is managed by the Netherlands Comprehensive Cancer Organisation (IKNL).

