## Methods/design

### Aim of this study

The UMBRELLA Fit study follows the cmRCT design (see Additional file 1). Here, patients with breast cancer who participate in the UMBRELLA breast cancer cohort (Utrecht cohort for Multiple BReast cancer intErvention studies and Long-term evaLuAtion) will be randomly selected for a 12-week supervised exercise intervention, 12 or 18 months after enrollment (i.e. postoperatively, prior to consultation of the radiation oncologist) in the UMBRELLA cohort. The purpose of the UMBRELLA Fit study is twofold. The first aim is to assess the feasibility and therefore, we will (1) assess the participation rate and intervention compliance in the intervention group and drop-out rates in the intervention and control group; (2) compare the (change in) physical activity levels in the intervention and control group during the intervention period; and (3) assess whether a more diverse generalizable study population will be included by comparing characteristics of the included study population with characteristics of patients participating in previous breast cancer exercise trials with a conventional RCT design. Our second goal is to examine the effectiveness of the exercise intervention on the QoL of patients with breast cancer in the short term (6 months) and long term (24 months).

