#### Methodological outcomes

To assess contrasts in physical activity levels between the intervention and control group, we will compare changes in physical activity levels within the control group to changes in the intervention group using analysis of covariance (ANCOVA) or mixed linear regression models adjusted for baseline for the analyses of repeated outcomes [38].

Participation rate, intervention compliance, retention and drop-out will be compared to findings in previous conventional exercise-oncology RCTs. For instance, a systematic review reported median (IQR) rates of uptake, adherence and completion of exercise programmes in patients with cancer of 63% (33–80%), 84% (72–93%) and 87% (80–96%), respectively [39]. More recent and relevant publications, if available, will also be taken into account. Comparisons will be done by using the chi-squared test or independent samples *t* test.

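### Setting one cmRCT against a pooled POLARIS patient total, with tests that carry no term for source trial, could let ordinary trial-to-trial variation pass for an effect of the cmRCT design

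*Protocol article*

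**What the plan says.** The third part of the feasibility aim (Aim of this study) is to find out whether the design yields a more diverse and generalizable population, by "comparing characteristics of the included study population with characteristics of patients participating in previous breast cancer exercise trials with a conventional RCT design".

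The Generalizability section lists what is compared, "socio-demographics (e.g. age, educational level and household status) and medical information", and gives the comparator as a number of patients drawn from a database of many trials: "characteristics of more than 3163 patients with breast cancer participating in exercise trials, available from the POLARIS database with individual patient data from 34" exercise-oncology trials. The section does not say how many of the 34 trials contributed patients with breast cancer. It names no test and does not mention source trial.

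Under Statistical analyses, Methodological outcomes, participation, compliance, retention and drop-out are to be compared with earlier conventional trials. A systematic review is cited as an example, with a median uptake of 63% (interquartile range 33 to 80%). The paragraph closes: "Comparisons will be done by using the chi-squared test or independent samples" t test. Patient characteristics are not in that list, but no other method for comparison with outside trials appears in the article.

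**The concern.** Aim 3 is directed at the trial design, and on that question the study supplies a single observation: one cmRCT, set against a number of conventional trials. Trials differ from one another in age, education, stage, treatment and comorbidity because they differ in centre, period, country and entry criteria. A chi-squared or t test against the pooled patients counts only variation between patients. Its standard error shrinks with the number of patients, so a further conventional trial compared with the same pool would often differ significantly as well.

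At stake is the feasibility conclusion. A difference that any single trial might show could be credited to the cmRCT design. The allocation, the sample size and the quality-of-life analysis are not affected.

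**Working it through.** **Inputs from the protocol article.** Pool: N = 3163 patients (Generalizability). Trials in the database: 34 (Generalizability). UMBRELLA Fit: 83 per group, so 2 × 83 = 166 randomized (Sample size calculation). Expected attendance: 70%, so about 0.70 × 83 = 58 patients who accept. Uptake in earlier programmes: median 63%, interquartile range 33 to 80% (Methodological outcomes).

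**Assumed inputs.** The intraclass correlation ρ, meaning the share of a characteristic's variance that lies between trials, is varied from 1 to 10%. The number k of trials behind the 3163 patients is taken as 34, with 10 as a check. Trials are of equal size in the formula. The 5% level is the one in the sample size section; the article sets none for this comparison.

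**The plan's own figure.** The article gives no figure for this comparison. The 83 per group used here does reproduce. With difference 13 − 6 = 7 and pooled SD √((17.7² + 17.1²)/2) = 17.40, the normal formula gives 97.02, rounded up to 98; then 98 × 0.84 + 1 = 83.3, that is 83.

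**Error of a pooled test.** Take a characteristic with total variance 1, m patients in UMBRELLA Fit, and no design effect.

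- Variance the pooled test assumes: V0 = 1/m + 1/N
- Actual variance: V = (1 − ρ)·V0 + ρ·(1 + 1/k)
- Actual error of the nominal 5% test: 2·[1 − Φ(1.96·√(V0/V))]

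Worked case, m = 166, k = 34, ρ = 0.05:

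- V0 = 1/166 + 1/3163 = 0.00634
- V = 0.95 × 0.00634 + 0.05 × (1 + 1/34) = 0.0575
- 1.96 × √(0.00634/0.0575) = 0.651, so the error is about 51.5%

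All cases with k = 34:

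| ρ | m = 166 (all randomized) | m = 83 (one arm) | m = 58 (acceptors) |
|---|---|---|---|
| 0.01 | 22.5% | 14.7% | 11.9% |
| 0.02 | 34.0% | 22.8% | 18.2% |
| 0.05 | 51.5% | 38.6% | 32.0% |
| 0.10 | 63.6% | 51.9% | 45.1% |

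With k = 10 and m = 166, the values for ρ = 0.01 to 0.10 run from 23.5% to 64.6%, so the unknown number of contributing trials matters little. The term ρ(1 + 1/k) cannot fall below ρ however many POLARIS patients are added.

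A simulation with unequal trial sizes (m = 166, k = 17 and 34, 4000 runs per setting) agrees: about 22 to 66% for the t test and 23 to 68% for the chi-squared test over the same range of ρ.

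**The rates, mainly from the protocol's own figures.** Suppose uptake among the 83 patients offered the programme is tested against a fixed 63%.

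- Standard error: √(0.63 × 0.37/83) = 0.053
- Flagged when more than 1.96 × 0.053 = 0.104 away, that is outside about 53 to 73%

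By the definition of an interquartile range, a quarter of the reviewed rates lie at or below 33% and a quarter at or above 80%. So about half or more of them fall where a trial of this size would be flagged as different from the median of its own kind. Part of that spread is sampling error in the reviewed trials, so this illustrates wide variation and does not estimate ρ.

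**Cost of counting the trial as a source of variation.** The difference detectable with 80% power is (1.96 + 0.84)·√V. For m = 166 and k = 34 it is 0.22 SD if trial is ignored, 0.36 SD at ρ = 0.01, 0.46 SD at ρ = 0.02 and 0.67 SD at ρ = 0.05.

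**The case against.** A reader might infer that the protocol tests generalizability by treating the POLARIS patients as one sample, and that a significant result will be reported as an effect of the design. The article supports neither. The Generalizability section speaks only of comparing, with no test, threshold or decision rule. The sentence naming the tests follows a list of rates from which patient characteristics are absent. Nowhere is it said that a difference will be attributed to the design. The POLARIS data are at individual-patient level, so an analysis that keeps source trial is compatible with the text, and a fuller analysis plan may contain one. All of this stands, and it limits the point to a risk.

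It can also be said that the size rests on assumed values of ρ and k, and that 166 is the largest possible m, since the article does not define the study population for this comparison as all randomized, one arm or acceptors. That stands too, which is why the smaller m are shown. The inflation is lower there but remains well above 5%.

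Finally, no trial-level method can separate the design from this trial's own features: a radiotherapy cohort at one centre, inactive patients, 12 or 18 months after enrollment. This is correct, and it belongs in the protocol as a stated limit.

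The claim that only routine analysis-plan detail is missing does not stand. The comparator is described as a patient total, and the only tests named for outside comparisons ignore source trial. Even a purely descriptive comparison with one pooled mean or percentage hides the spread needed to judge whether one trial is unusual.

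**Conclusion.** The concern holds as a conditional one. If the named tests are applied to the patient characteristics, as their heading suggests but does not state, ordinary trial-to-trial variation could be read as a consequence of the cmRCT design. For ρ of 1 to 10% and 34 trials, the actual error of a nominal 5% test is about 22 to 64% with 166 patients, 15 to 52% with one arm of 83, and 12 to 45% with about 58 acceptors. The documents do not determine ρ, k or m, so these are ranges under assumptions. That conventional trials vary is supported by the article itself: uptake is quoted with an interquartile range of 33 to 80%, and the Background says that refusal is related to age, fatigue and comorbidity and willingness to education. The same weakness applies directly to the rates, for which the tests are stated. The change is worth making, but it concerns the feasibility aim only.

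**What to change.** In Generalizability and in Methodological outcomes, replace a pooled chi-squared or t test with a trial-level comparison. For each characteristic, show the UMBRELLA Fit value against the distribution of values in the POLARIS trials that contributed patients with breast cancer, using a model with a random trial effect or a 95% prediction interval for a new trial. Treat participation, compliance, retention and drop-out likewise, against trial-level rates. Say which UMBRELLA Fit patients form the compared population. Add that one cmRCT cannot separate the design from its own eligibility criteria and setting.

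The change needs analysis wording only, with no new patients or measurements; individual patient data should already carry a trial identifier. The price is sensitivity: with 166 patients and 34 trials, the detectable difference rises from 0.22 SD to about 0.36 to 0.67 SD for ρ of 1 to 5%. Fewer characteristics will be called different, and a real gain in diversity could go undetected.

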##### Trial retention

Retention will be scored as the rate of drop-out in the intervention group after signing informed consent for the UMBRELLA Fit study.

##### Cohort retention

Drop-out in the intervention and control group will be defined as withdrawal from the UMBRELLA cohort and/or non-response to the regular cohort measurements and will be scored for both groups.

#### Effectiveness endpoints

We will use the regular questionnaire measurements of the UMBRELLA cohort to assess QoL, fatigue, anxiety and depression, and sedentary behaviour. Patients are included 12 or 18 months after enrollment in the UMBRELLA cohort. The most recent questionnaires filled in before enrollment in the UMBRELLA Fit study will serve as baseline measurements. Questionnaires 6 and 24 months later will be used as follow-up measurements.

##### Quality of life

The European Organisation for Research and Treatment of Cancer Quality of Life Questionnaire C30 (EORTC QLQ-C30) is a 30-item questionnaire to assess the quality of life of patients with cancer [30]. The questionnaire comprises five functional scales (physical, role, emotional, cognitive and social), three symptom scales (fatigue, pain and nausea/vomiting) and a global health status/QoL scale.

Sedentary time will be assessed by two questions from the IPAQ questionnaire estimating weekly sitting time [31].

##### Anxiety and depression

Anxiety and depression will be assessed using the validated Dutch language version of the Hospital Anxiety and Depression Scale (HADS) [32]. This questionnaire consists of seven items for the depression subscale and seven items for the anxiety subscale, resulting in a total depression score and a total anxiety score.

### Additional measurements for the patients in the intervention group

Patients in the intervention group will visit the UMC Utrecht for additional measurements at the start and end of the intervention. These measurements include anthropometrics, cardiopulmonary exercise testing (CPET) and questionnaires to assess QoL, fatigue and physical activity (also completed with the regular measurements in the UMBRELLA cohort).

#### Anthropometrics

Body weight and height will be measured while patients wear light clothes and no shoes. A digital balance is used to measure weight (to the nearest 0.1 kg) and wall-mounted tape to measure height (to the nearest 0.1 cm). Body fat distribution will be assessed by the waist and hip circumference (to the nearest 0.5 cm) in duplicate and averaged. Waist circumference is measured while standing, midway between the lower ribs and the iliac crest. Hip circumference is measured across the buttocks, while standing.

#### Cardiorespiratory fitness

To determine cardiorespiratory fitness, peak oxygen uptake (VO2_peak_) and anaerobic threshold will be assessed by a CPET using a cycle ergometer and a ramp protocol. Expired gases and minute ventilation and heart rate will be monitored continuously. The CPET is performed under medical supervision. The patient will be verbally encouraged in a standard manner. A CPET is safe for patients with cancer and we will adhere to the recommendations for testing procedure and safety [33]. Blood pressure will be measured with an automatic tonometer at rest and regularly during cycling. Also, an electrocardiogram (ECG) will be performed at rest and will be monitored continuously during the CPET.

#### Self-efficacy

Exercise-related self-efficacy will be assessed at baseline by six items, based upon SCT [29]. Items will be scored on a 5-point Likert scale with endpoints labelled “strongly disagree” and “strongly agree”.

#### Adherence and compliance

To monitor physical activity, patients are asked to keep a daily physical activity log to register the frequency and duration of activities they perform. They also register how many times the Jawbone UP2™ vibrates and their behaviour as the result of an alert. To determine adherence to the exercise intervention, attendance rate for the training sessions and compliance with the protocol (i.e. training intensity and duration according to protocol) will be recorded by the physiotherapist. Adherence to an active lifestyle will be monitored by the physiotherapist by two-weekly evaluations of the daily physical activity log.

### Statistical analyses

#### Sample size calculation

The sample size calculation is based on the intention-to-treat analyses of the primary effectiveness outcome QoL (EORTC-QLQ-30) [30]. Here, we determine a clinically relevant difference as a difference of 10 points [30]. A difference of 10 points is realistic because in a previous exercise trial in patients with cancer, QoL in the intervention group improved by 15.1 points (SD 17.7) and in the control group by 6.1 points (SD 17.1) using the EORTC-QLQ-30 after the 12-week intervention [34, 35]. Therefore, using the control group data from the previous trial and the 10-point difference, we assume a 6-point increase in QoL in the control group and a 16-point increase in the intervention group, among patients who accept the intervention in this cmRCT. We expect an attendance rate of 70% in the intervention group and assume that the improvement in non-attenders randomized to the intervention group (30%) is equal to the improvement in the control group (i.e. 6 points). Furthermore, we assume that non-attendance does not impact the standard deviation. As a result, we estimate a mean improvement of 13 points in the intervention group ((70*16 + 30*6)/100 = 13) instead of 16 points and a mean improvement of 6 points in the control group. Using these numbers, standard deviations of 17.7 and 17.1, power of 80% and alpha of 0.05, we calculated that 98 patients are needed in each group.

As we will use linear regression analyses adjusted for baseline, the correlation between baseline and follow up needs to be taken into account in the sample size calculation. Therefore, the calculated number of subjects should be multiplied by (1-*ρ*
^2^), plus one extra subject per group [36], where *ρ* represents the correlation between baseline and follow-up outcomes. In our previous trials [34, 35], we identified correlation of 0.4 between baseline and follow-up QoL. This leads to a final sample size of 83 patients per group (98*0.84 + 1). As recommended by Candlish [37], we will update the sample-size calculation before the end of the trial when the actual acceptance rate of the intervention deviates from the estimated rate and adapt the sample size accordingly.

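### The baseline-adjustment factor of 0.84 fits follow-up SDs, but is applied to a sample size built on SDs of improvement, so 83 per group and 80% power do not follow from the stated inputs

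*Protocol article*

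**What the plan says.** All the relevant text is in the protocol article, Statistical analyses, Sample size calculation.

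- Basis: "The sample size calculation is based on the intention-to-treat analyses of the primary effectiveness outcome QoL (EORTC-QLQ-30").
- Source of the SDs: in a previous trial, "QoL in the intervention group improved by 15.1 points (SD 17.7) and in the control group by 6.1 points (SD 17.1"). The SDs are attached to improvements. No baseline or follow-up SD is given.
- Effect: with 70% attendance, "we estimate a mean improvement of 13 points in the intervention group ((70*16 + 30*6)/100 = 13) instead of 16 points". The control group is assumed to improve by 6, so the difference in mean improvement is 7 points.
- First result: with "standard deviations of 17.7 and 17.1, power of 80% and alpha of 0.05, we calculated that 98 patients are needed in each group".
- Adjustment for baseline: the number is multiplied by 1 − ρ², plus one subject per group. The plan defines ρ as the correlation of baseline with follow-up outcomes and takes it as 0.4 from the previous trials. "This leads to a final sample size of 83 patients per group (98*0.84 + 1").
- Simplification: "we assume that non-attendance does not impact the standard deviation".
- Update: the calculation will be revised before the end of the trial if the acceptance rate differs from the expected rate.

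The Effectiveness outcomes section plans intention-to-treat linear regression adjusted for baseline, which is the analysis that the adjustment is meant to reflect.

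**The concern.** The factor 1 − ρ² converts a sample size for comparing follow-up scores into one for a baseline-adjusted comparison. A sample size built on SDs of change already uses the baseline once, through the subtraction, and needs a different factor. The plan feeds change SDs and a difference in mean change into the first step, then applies the follow-up factor in the second. No step converts one kind of SD into the other.

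At stake is whether the stated size and power for the primary effectiveness outcome belong together. It also matters for the planned update: if the same recipe were used again with other inputs, the error would pass into the revised target, and its direction could change.

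**Working it through.** **Inputs** (all from the Sample size calculation section): SDs 17.7 and 17.1, difference 13 − 6 = 7, alpha 0.05, power 80%, ρ = 0.4. Sidedness is not stated. Two-sided reproduces the plan's figure; one-sided gives 77 and does not.

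**1. The plan's own figures reproduce.**
- Pooled variance: (17.7² + 17.1²)/2 = 302.85, so SD = 17.40.
- n = 2 × 302.85 × (1.960 + 0.842)²/7² = 97.02 by the normal approximation, and 97.99 with the t distribution. Both round up to 98.
- 98 × (1 − 0.4²) + 1 = 98 × 0.84 + 1 = 83.32, stated as 83.

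**2. The factor that matches a change SD.** Let baseline and follow-up have the same SD σ (an assumption, since the article gives neither).
- Variance of change: 2σ²(1 − ρ).
- Residual variance after adjusting for baseline: σ²(1 − ρ²).
- Ratio: (1 − ρ²)/[2(1 − ρ)] = (1 + ρ)/2 = 0.70 at ρ = 0.4.

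**3. Size and power with that factor.**
- 98 × 0.70 + 1 = 69.6, so 70 per group for 80% power.
- Residual SD: 17.40 × √0.70 = 14.56. Power at 83 per group: 86.8% (t) or 87.2% (normal).
- If the SDs are of follow-up scores, the factor 0.84 applies, and power at 83 is 80.3% (t) or 80.7% (normal).

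**4. Dependence on the equal-SD assumption.** With k = follow-up SD/baseline SD, the factor on a change-based n is k²(1 − ρ²)/(1 + k² − 2ρk). At ρ = 0.4:

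| k | factor | 98 × factor + 1 | power at 83 (normal) |
|---|---|---|---|
| 0.8 | 0.538 | 53.7 | 94% |
| 0.9 | 0.624 | 62.2 | 91% |
| 1.0 | 0.700 | 69.6 | 87% |
| 1.1 | 0.764 | 75.9 | 84% |
| 1.25 | 0.840 | 83.3 | 81% |
| 1.5 | 0.922 | 91.4 | 77% |

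With change SDs, the stated 83 and 80% agree only at a ratio near 1.25.

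**5. Dependence on ρ (equal SDs).** The two factors are equal when 1 − ρ² = (1 + ρ)/2, that is at ρ = 0.5, where both are 0.75. Below that the plan's recipe gives too many patients, above it too few. At ρ = 0.6 the recipe gives 98 × 0.64 + 1 = 63.7 (64), against 98 × 0.80 + 1 = 79.4 (80) needed, and power at 64 is about 71–72%.

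**6. Sensitivity: the attendance mixture.** A group with 70% at +16 and 30% at +6 has extra variance 0.7 × 0.3 × 10² = 21.
- With SD 17.7 for everyone in the arm: √(17.7² + 21) = 18.3.
- With the control SD for non-attenders: √(0.7 × 17.7² + 0.3 × 17.1² + 21) = √328.0 = 18.1.
- Power at 83 (t) falls from 86.8% to 85.7–86.0% with factor 0.70, and from 80.3% to 78.9–79.3% with factor 0.84. These figures let baseline adjustment shrink the added variance by the same factor.

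**The case against.** Four points can be made for the plan.

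- **The SDs may be follow-up SDs, mislabelled in the sentence.** Then 0.84 is right and 83 stands. Only the previous trials' data can settle this. The point stands as a limit on certainty, but the text would still need correcting, because it attaches the SDs to improvements.
- **The factor 0.70 needs equal baseline and follow-up SDs.** This stands. The article gives neither SD, and at a ratio near 1.25 the plan's figures agree even with change SDs. The 87% is one value in a range.
- **In the equal-SD case the error is on the safe side.** This also stands. A reader might infer from a wrong factor that the trial is underpowered. The stated inputs do not support that: at ρ = 0.4 with equal SDs, 83 is more than needed. Power falls below 80% at 83 only if the follow-up SD exceeds the baseline SD by more than about a quarter, which the article does not say. The planned analysis itself is unaffected.
- **The assumption that non-attendance leaves the SD unchanged is declared openly.** A reader might count it as a second error, because the mean is computed from a 70/30 mixture. It is a stated simplification worth about one percentage point of power, and not a separate error.

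A reader might also infer that the sample-size update is bound to repeat the mismatch. The article commits to an update when acceptance deviates, but does not fix the formula for it.

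**Conclusion.** The concern holds in limited form. As written, the calculation combines SDs of improvement with a factor that belongs to follow-up SDs, so 83 per group and 80% power do not follow from the stated inputs. With change SDs, ρ = 0.4 and equal baseline and follow-up SDs, 80% power needs about 70 per group, and 83 give about 87%: a gap of 13 per group, or about 7 percentage points, on the conservative side. The size and sign of the gap rest on the unreported SD ratio and on ρ. The documents show neither that the trial is underpowered nor, if the SDs prove to be follow-up SDs, that 83 is the wrong number. They do show that either the factor or the description of the SDs has to be corrected.

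**What to change.** 1. Check in the previous trials' data whether 17.7 and 17.1 are SDs of change or of follow-up scores.
2. If change: compute the residual variance of the baseline-adjusted analysis from the observed baseline SD, follow-up SD and ρ; this reduces to the factor (1 + ρ)/2 if the SDs are equal. Keep 83 per group and restate the power, about 87% under equal SDs.
3. If follow-up: correct the sentence that attaches the SDs to improvements and keep 0.84.
4. Use the matching formula in the planned sample-size update, and state in advance which SDs and which ρ it takes.
5. Optionally, report as a sensitivity that an intervention-arm SD of 18.1–18.3 lowers power by about one percentage point.

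The cost is one look at existing data, one recalculation and a short text correction, with no extra enrolment.
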